## Abstract

**Background:**

In Denmark 8,000 to 10,000 people will attempt suicide each year. The Centre of Excellence in Suicide Prevention in the Capital Region of Denmark is treating patients with suicidal behavior, and a recent survey has shown that 30% of the patients are suffering from borderline personality disorder. The majority of patients (70% to 75%) with borderline personality disorder have a history of deliberate self-harm and 10% have a lifetime risk to die by suicide. The DiaS trial is comparing dialectical behavior therapy with collaborative assessment and management of suicidality-informed supportive psychotherapy, for the risk of repetition of deliberate self-harm in patients with a recent suicide attempt and personality traits within the spectrum of borderline personality disorder. Both treatments have previously shown effects in this group of patients on suicide ideation and self-harm compared with treatment as usual.

**Methods/Design:**

The trial is designed as a single-center, two-armed, parallel-group observer-blinded randomized clinical superiority trial. We will recruit 160 participants with a recent suicide attempt and at least two traits of the borderline personality disorder from the Centre of Excellence in Suicide Prevention, Capital Region of Denmark. Randomization will be performed though a centralized and computer-generated approach that conceals the randomization sequence. The interventions that are offered are a modified version of a dialectical behavior therapy program lasting 16 weeks versus collaborative assessment and management of suicidality-informed supportive psychotherapy, where the duration treatment will vary in accordance with established methods up to 16 weeks. The primary outcome measure is the ratio of deliberate self-harming acts including suicide attempts measured at week 28. Other exploratory outcomes are included such as severity of symptoms, suicide intention and ideation, depression, hopelessness, self-esteem, impulsivity, anger, and duration of respective treatments.

**Trial registration:**

Clinical Trial.gov: NCT01512602.

## Background

In Denmark, the suicide rate is 11.9 per 100,000 people per year according the World Health Organization
[1]. Around 8,000 to 10,000 people attempt suicide each year based on information registered in the National Patient Register and the Register of Suicide. Patients who attempted suicide have an increased risk of recurrent suicide attempts and suicidal death
[2]. Borderline Personality Disorder (BPD), according to the DSM-IV
[3], affects approximately 1% to 2% of the general population, and this patient group represents up to 10% of all psychiatric outpatients and 20% of all inpatients
[2,4]. A total of 60% to 70% of the patients with borderline personality disorder will attempt suicide, and the lifetime risk of death by suicide is as much as 10%
[5], a risk 50 times higher than in the general population. Approximately 70% to 75% of individuals with BPD, a condition which is associated with challenges in regulating emotions and difficulties in tolerating emotional distress
[6], exhibit nonsuicidal self-harm
[6].

Dialectical behavior therapy is a manual-based treatment, which was originally developed by the American psychologist Marsha Linehan
[6] for the treatment of the core problems of patients with borderline personality disorder, especially concerning emotional regulation, which makes patients particularly prone to self-harming acts. The treatment has shown positive effect in several randomized trials to reduce the high risk of self-injury and suicide attempt in patient with BPD compared with treatment as usual
[7-12]. A recent meta-analysis has shown DBT to be the most evidence-based psychotherapeutic treatment for borderline personality disorder and can reduce numbers of self-harming acts and related secondary markers compared with other psychotherapeutic treatments, for example, cognitive behavioral therapy and interpersonal psychotherapy
[13]. DBT has also shown effect in treating other dysfunctions such as drug dependence
[14] and eating disturbances
[15]. A recent systematic review
[16] describes seven different studies where the DBT treatment duration varies from 3 to 12 months, and indicates that the most treatment gain is made during the first 4 months of treatment.

The collaborative assessment and management of suicidality (CAMS)-informed supportive psychotherapy was developed by [name] and has been somewhat modified in conjunction with Danish colleagues for this study. CAMS is considered both a philosophy of care and a clinical therapeutical framework
[17-19]. As a flexible therapeutical framework, CAMS is trans-theoretical and can thereby by used across theoretical orientations, clinical techniques, and professional disciplines. CAMS is designed to specifically target suicidal ideation and behavior as the central clinical focus, independent of diagnosis. Through collaborative assessment and deconstruction of the patient’s suicidality, key problems and goals naturally emerge. Collaborative treatment planning that follows thus creates a problem-focused approach that is designed to reconstruct more viable ways of coping and living. Early studies of CAMS have shown positive effects in reducing suicide ideation in smaller studies with suicidal patients on several parameters
[19-23], but there is a need for further research in well-powered clinical trials
[24].

The two interventions - DBT versus CAMS - have been chosen for the DiaS trial. They have not previously been compared head to head. This trial will target patients with borderline personality traits and recent suicide attempts.

## Methods/Design

Our plan is to compare 16 weeks treatment of DBT versus CAMS. The primary outcome will be the ratio of participants with suicide attempts or non-suicidal deliberate self-harming acts (self-reported and registered in medical records) during the treatment period in the treatment period and at follow-up until week 28 after randomization.This trial is designed as a single-center, two-armed, parallel-group, observer-blinded randomized clinical superiority trial (Figure 
1).

**Figure 1 F1:**
[figure not shown]
The flowchart of the recruiting and randomization in the DiaS trial.

### Recruitment and criteria for inclusion and exclusion

The patients are recruited through the Centre of Excellence for Suicide Prevention, Capital Region of Denmark. This is a highly specialized outpatient care center treating 450 patients annually and offering short-term supportive psychotherapy and social counseling. The patients are referred from general practitioners and from somatic and psychiatric wards after suicide attempts; patients can also self-refer to the Centre. The patients will be referred to the trial and screened by an assessor. If the patients fulfill the inclusion criteria and none of the exclusion criteria (see list of inclusion and exclusion criteria below), they be will included in the trial and randomized by the first contact therapist in the Centre of Excellence for Suicide Prevention. In the screening interview patients will be subjected to a Mini International Neuropsychiatric Interview (MINI)
[25] and a Structured Clinical Interview for DSM-IV Axis II Personality Disorders
[26]. Deliberate Self-Harm (DSH) and recent suicide attempts will be measured by using Lifetime Suicide and Self-Injury (L-SASI)
[27] and Suicide Attempt and Self-injury Interview (SASII)
[28]. The therapist will contact the patients and inform them of which group of the treatment they are to be allocated. The adherence to the treatments in both groups will be measured continuously. Follow-up interviews are performed in week 17, 28, and 52 after inclusion

### Inclusion and exclusion criteria in the DiaS trial

#### Inclusion criteria

1) 18 to 65 years of age.

2) Recent suicide attempt within one month from the inclusion date.

3) At least two of the following criteria for borderline personality disorder (DSM-IV)^a^:

a) Desperate efforts to avoid being betrayed or abandoned in reality or in imagination.

b) A pattern of unstable and intense interpersonal relationships characterized by a swinging between extremes of idealization and devaluation.

c) Identity disturbance: markedly and persistently unstable self-image or self-feeling.

d) Impulsivity in at least 2 areas that are potentially self-harming (for example, sexual misconduct, abuse, consumption, and overeating).

e) Repeated instances of suicidal behavior, gestures or threats or self-harm.

f) Affective instability.

g) Chronic feelings of emptiness.

h) Inappropriate intense anger or difficulty controlling anger.

i) Transient, stress related paranoid ideation, delusions or severe dissociative symptoms.

4) Informed consent.

#### Exclusion criteria

– Severe depression.^b^

– Bipolar disorder.^b^

– Psychosis in schizophrenia spectrum.^b^

– Anorexia nervosa.^b^

– Alcohol or drug addiction.^b^

– Mental retardation.

– Dementia.

– Insufficient ability in speaking and understanding Danish

– Lack of informed consent.

^a^Assessed by SCID-II
[26].

^b^Assessed by Mini International Neuropsychiatric Interview (MINI)
[25].

All psychiatric departments in the Capital region of Denmark have been informed of the DiaS trial through meetings and leaflets (see inclusion criteria above). Patients with at least two traits from the BPD diagnosis (DSM-IV)
[3] and a recent suicide attempt are referred through the Centre of Excellence in Suicide Prevention. The suicide attempt has to be within a month from the first contact with the Centre. The date has been selected to ensure the accuracy of reporting the intent and other important circumstances (feelings, thoughts and behavior prior to, at the time of, and after the suicide attempt). The patients must speak and understand Danish sufficiently to participate in the therapy sessions and the assessment of the trial. The diagnostic criteria for exclusion have been chosen to eliminate potential confounders in the trial and ensure a homogenous group of patients.

### Randomization and blinding

Patients will be randomized into one of two treatment arms. The randomization is stratified by sex and previous number of self-harm acts (one versus multiple). This is done to avoid the risk of patients with multiple self-harm acts being overrepresented in one of the treatment groups. The Copenhagen Trial Unit (CTU) will generate a computer-generated random sequence randomization, using alternating block sizes unknown to the investigators. The trial staff will contact the CTU for information about allocation. The above-mentioned procedure ensures adequate allocation concealment. The patients and therapists will not be blinded. We will use blinded outcome assessors (see outcomes below).

### Dialectical behavior therapy

Dialectical behavior therapy (DBT) consists of four components: 1) individual therapy, 2) skills training in groups, 3) access to telephone contact with therapists, and 4) supervision and consultations for the therapist to prevent burn-out. The first aim of the therapy is organized around a target hierarchy, which consists of 1) eliminating life-threatening behavior including suicide attempts and deliberate self-harm, 2) eliminating treatment interfering behavior such as non-attendance and not doing homework, and 3) ameliorating behaviors leading to a decreased quality of life (axis I disorders, social aspects, and drug dependence). The second aim of the therapy is skill training in groups. Patients are taught four modules of primary skills: 1) mindfulness, 2) emotional regulation, 3) distress tolerance, and 4) interpersonal effectiveness. The individual therapy will focus on the taught skills in the groups. The DBT treatment manual is based on DBT-A by Rathus and Miller
[29]. The DBT intervention will consist of 16 weeks treatment defined as 2 hours weekly skill training in groups, 1 hour weekly individual psychotherapy, opportunity of telephone coaching with the therapist, and approximately 1 hour weekly team consultation and supervision.

### Collaborative assessment and management of suicidality-informed supportive psychotherapy

The second intervention consists of supportive psychotherapeutic treatment within the framework of CAMS. CAMS-informed supportive psychotherapy is a psychotherapeutic approach based on principles from the ‘Collaborative assessment and management of suicidality’
[19]. The method typically employs a 45- to 60-minute session once a week in the office of the therapist (in crisis situations the length, frequency, and location of care may vary). CAMS sessions have a specific structure starting in the first 10 to 20 minutes with a collaborative working through of the ‘core assessment’ of the ‘Suicide Status Form’ (SSF), rating on a scale of 1 to 5 the following six suicide-related markers: psychological pain, stress, agitation, hopelessness, self-hate, and overall risk of suicide. In the collaborative exploration of these and additional SSF constructs, the patient and the therapist sit side-by-side. Following the initial assessment, various ‘drivers’ of suicidality are identified and further investigated. Direct drivers are thoughts, feelings, behaviors and interpersonal themes that lead to suicidal thoughts and acts. Indirect drivers are other factors that contribute but do not directly lead to suicidal ideation or feelings, such as: unemployment, depression, substance abuse, post-traumatic stress disorder. A treatment plan is collaboratively formulated that emphasizes a ‘crisis response plan’ to establish outpatient stability. In addition, the CAMS treatment plan further identifies, targets, and treats suicidal drivers with problem-focused interventions. On-going CAMS care involves the development of coping skills for emergencies (for example, the elaboration and use of a crisis response plan) as well as the on-going linking of drivers and suicidality and problem-focused interventions that treat those issues that makes the patient suicidal. This philosophical and clinical approach to treatment is used in subsequent CAMS sessions as the problem-focused treatment to ultimately eliminate suicidal coping as much as possible.

The duration of the CAMS treatment differs depending on the patient’s suicidality. The therapist concludes CAMS treatment after three successive contracts where the patient is assessed to be non-suicidal according to the SSF criteria
[17]. In this study, the therapists are supervised one and a half hours every second week.

### Assessments

The patients will be subjected to four almost identical assessments. The first baseline assessment will be performed in continuity with the assessment and validation of the inclusion and exclusion criteria. Also the strata used for the randomization will be obtained in the first interview with the patient. The second assessment will occur after treatment has ended in week 17 after inclusion in the trial. The third and fourth assessment will occur at a follow-up interview after week 28 and week 52 after inclusion.

### Outcomes

#### Primary outcome

The primary outcome will be measured as the ratio of deliberate self-harm before and after treatment (week 0 compared with week 28). The Suicide attempt and Self-Injury Interview (SASII)
[28] will be used to collect these data and direct questions in the follow-up interview regarding self-harming behavior after inclusion in the trial. We will also obtain information concerning numbers of deliberate self-harm and suicide attempts through medical records.

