### Sample size and statistical analyses

Based on previous estimations, we expect the risk of renewed self-harming acts within their first year to be 50 percent in the CAMS treatment group
[6]. We expect the DBT to be able to reduce this risk to 25 percent, a relative risk reduction of 50%. With a power of 90% and a type one error probability associated with this test of 0.05, we plan to randomize 154 patients, with about 77 patients in each intervention group. We will handle missing data using logistic regression with multiple imputations as described below.

The two group baseline characteristics will be compared using Student’s *t*-test for independent samples or a chi-square test for binary variables.

The primary analysis will be based on the intention-to-treat principle; that is, data from all patients will be included in the treatment group to which they were allocated regardless of degree of compliance.

Binary outcomes will be analyzed using logistic regression and continuous outcomes will be analyzed using linear regression with baseline variables as sex and previous deliberate self-harm as a covariates.

If more than 5% of the primary outcome is missing at follow-up, we will use multiple imputations (SPSS version 19.0). If this is the case, the multiple imputations will be considered the primary result. For multiple imputations, we will use a linear regression model with 100 imputations and 20 iterations. The pooled estimates from the imputations will subsequently be used for our analysis.

We will use two-tailed tests for statistical significance with alpha set at *P* <0.05.

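### The primary outcome is stated inconsistently, and the sample size matches only the participant-level version in type, using one-year risks for a 28-week outcome

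*Protocol article*

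**What the plan says.** All the wordings below are current text of the protocol article.

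- **Abstract, Methods/Design:** "The primary outcome measure is the ratio of deliberate self-harming acts including suicide attempts measured at week 28". The unit is the act.
- **Methods/Design (main text):** "The primary outcome will be the ratio of participants with suicide attempts or non-suicidal deliberate self-harming acts", counted over the treatment period and "at follow-up until week 28 after randomization". The unit is the participant.
- **Outcomes, Primary outcome:** "The primary outcome will be measured as the ratio of deliberate self-harm before and after treatment (week 0 compared with week 28". This is a before/after contrast, and its unit is not stated.

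Sample size and statistical analyses plans on participant-level risks: "we expect the risk of renewed self-harming acts within their first year to be 50 percent in the CAMS treatment group", and then "We expect the DBT to be able to reduce this risk to 25 percent, a relative risk reduction of 50"%. Power is 90%, with "a type one error probability associated with this test of 0.05" and two-tailed tests, giving 154 patients, about 77 per arm. The section assigns logistic regression to binary outcomes and linear regression to continuous ones, with sex and previous self-harm as covariates. It names no model for counts or rates.

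**The concern.** Two things differ between the wordings: the unit (act or participant) and the contrast (between arms after randomization, or before against after). A proportion of participants with any act, a number of acts and a change from baseline are different quantities. They need different models and need not give the same answer. The article therefore does not show which one carries the confirmatory test.

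The stated power belongs to one specific quantity. If another is analysed as primary, the 90% does not carry over. Even for the quantity that does fit, the planning risks cover a longer period than the outcome.

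**Working it through.** **1. Reproduce the planned size.** Inputs from Sample size and statistical analyses: p1 = 0.50, p2 = 0.25, two-sided alpha 0.05 (z = 1.960), power 90% (z = 1.282). With p̄ = 0.375 and the pooled-variance formula

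n = [1.960·√(2p̄(1−p̄)) + 1.282·√(p1(1−p1)+p2(1−p2))]² / (p1−p2)²

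the terms are √0.46875 = 0.6847 and √0.4375 = 0.6614, so n = (1.342 + 0.848)²/0.0625 = 76.7. That is **77 per arm, 154 in total**, as stated, with power 90.1% at 77 per arm. The calculation is a comparison of two independent proportions of participants.

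**2. Match each wording to that calculation.**

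| Wording | Unit | Contrast | Matches 50% v 25% in type? |
|---|---|---|---|
| Methods/Design | participant | between arms, to week 28 | yes |
| Primary outcome | not stated | week 0 v week 28 | only if read at participant level |
| Abstract | act | at week 28 | no, if taken literally |

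**3. The before/after wording at participant level.** A suicide attempt within one month is an inclusion criterion. For any baseline look-back that reaches that attempt, the week 0 proportion is 100% in both arms. At the plan's risks, after/before is 50%/100% = 50% for CAMS and 25%/100% = 25% for DBT. The difference between arms is 25 points, exactly as in Methods/Design, so the clause adds nothing.

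**4. The before/after or act wording at act level.** The article gives no mean count, dispersion, SD or before/after correlation, so no power follows from it. The illustration below shows how far the answer depends on assumptions. It takes negative binomial counts, the control mean set so that 50% of CAMS patients have no act, SE of the log rate ratio = √[(1/m1 + 1/m2 + 2k)/77], and dispersion k assumed.

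| k | Power at 77 per arm if the rate is halved | Power if 25% of DBT patients have any act |
|---|---|---|
| about 0 | 83% | 94% |
| 1 | 78% | 98% |
| 2 | 70% | 99% |
| 4 | 54% | over 99% |

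The range runs on both sides of 90%.

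**5. Time window for the version that fits.** The 50% and 25% are risks over the first year; the outcome ends at week 28. Assuming a constant hazard over 52 weeks:

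- CAMS: 1 − 0.50^(28/52) = 31.1%
- DBT: 1 − 0.75^(28/52) = 14.4%
- Power at 77 per arm: about **70%**; 129 per arm would be needed for 90%.
- Keeping the 50% relative reduction instead (31.1% v 15.6%): about **63%**; 154 per arm would be needed for 90%.

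**The case against.** Much can be said for the plan. Methods/Design itself uses the word ratio for a share of participants, so the abstract sentence may be a compressed form of the same outcome. The firm conflict is then between Methods/Design and the Primary outcome section. That is fair, but it leaves the conflict in place.

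The analysis section could be said to cover a ratio through linear regression for continuous outcomes. It also never names the primary outcome when it assigns logistic regression. The link between the two is therefore an inference, though the two-proportion sample size supports it strongly.

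Three stronger readings are tempting, and the article does not support them:

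- *The before/after outcome measures regression to the mean instead of treatment.* The trial is a randomized two-arm comparison, so a fall common to both arms cancels. It is likewise wrong to say that 50 of the 75 points of improvement under DBT are spurious, because no single-arm comparison is proposed.
- *A count outcome would be underpowered.* The table above shows that this depends wholly on assumed counts. The supported statement is that the 90% cannot be derived, not that power is lower.
- *The result will be chosen after the data are seen.* This is a condensed article, and an analysis plan not shown may fix the definition. The finding is that the published wordings disagree.

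**Conclusion.** The point holds as an internal contradiction in the definition of the primary outcome. The wording in the Primary outcome section cannot stand beside that in Methods/Design, and the abstract needs clarifying. Only the participant-level proportion matches the 154 patients and 90% power in outcome type. At act level the 90% is unsupported. At participant level the week 0 comparison is redundant.

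Aligning the definitions does not by itself restore the power claim. If 50% and 25% are one-year risks, as the text says, power for the 28-week outcome at 77 per arm is about 63% to 70%. That figure rests on a constant hazard, which the article neither states nor contradicts. If self-harm is concentrated soon after the index attempt, the 28-week risks would lie nearer the one-year risks and the loss would be smaller.

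**What to change.** 1. Use one definition in the abstract, Methods/Design and the Primary outcome section: the proportion of participants with at least one suicide attempt or non-suicidal self-harm act from randomization to week 28, compared between arms by logistic regression adjusted for sex and previous self-harm.
2. Delete the parenthesis in the Primary outcome section that sets week 0 against week 28, together with the before/after wording.
3. List the number of acts and the before/after change as exploratory.
4. In Sample size and statistical analyses, name the primary outcome explicitly. Restate the assumed risks for the 28-week window, and give the resulting power at 77 per arm.

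Items 1 to 3 cost wording only and need no new data. Item 4 costs one recalculation. If the 28-week risks are materially below 50% and 25%, the sponsor must either accept and report the lower power or plan a larger sample; under the constant-hazard assumption that means 129 to 154 per arm for 90%.
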